### Study objectives and outcome measures

The primary study objectives and outcome measures are:Assessment of treatment efficacy of imiquimod treatment for high-grade CIN, as compared to LLETZ treatment. Successful treatment for the experimental (imiquimod) arm is defined as regression to CIN 1 or less in diagnostic biopsies at 20 weeks follow-up. Successful treatment for the LLETZ arm is defined as normal cytology at 6 months follow-up. Based upon earlier studies, we hypothesize that 50–75 % of patients in the experimental (imiquimod) arm will show regression to CIN 1 or less.These two different outcome measures (cytology in the LLETZ arm and histology in the experimental arm) were selected in order to optimize the assessment of treatment efficacy, whilst limiting overtreatment of patients (performing unnecessary biopsies or LLETZ treatments). For the experimental arm, it is assessed by colposcopy with diagnostic biopsies and for the LLETZ arm it is assessed by cytology. Regarding efficacy of LLETZ treatment, the significance of resection margins of the LLETZ specimen is controversial and is not advised in guidelines as outcome measure of LLETZ efficacy. Therefore, regular follow-up cytology at six months was selected as outcome measure, as is also done in clinical practice. Regarding imiquimod treatment, histological assessment of treatment efficacy was selected as outcome measure, in order to optimize the assessment of potential residual disease. Biopsies were chosen rather than a standard LLETZ procedure to evaluate residual disease, to prevent overtreatment.Development of a biomarker model to predict adequate response to imiquimod treatment.

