### Data collection

Coded data are stored both on paper and in an electronic database. Collected data are stored in a digital case report form (CRF). Raw data is available only to the principal and coordinating investigator. The following data are recorded:

*Baseline*Patients characteristics: age, ethnical background, education, medical history, smoking, sexual behaviour.HPV genotyping.Histological biomarkers on biopsies of patients in the experimental arm: markers of lymphoproliferative response: CD4, CD8, CD25, CD138, fox p3; cell cycle markers: p16, Rb, p53, Ki67, CK 13, CK 14, IMP3.Quality of life.

*6 weeks follow-up*Adverse effects of imiquimod treatment: patient reported side effects and side effects noticed at clinical investigation.Adverse effects of LLETZ treatment: patient reported side effects, using a standardized report form.

*10 weeks follow-up*Treatment compliance: amount of applied doses of imiquimod, as documented by the study subject on a dose calendar.Histological presence and grading of CIN for the experimental arm.Adverse effects of imiquimod treatment: patients reported side effects and side effects noticed at clinical investigation.

*14 weeks follow-up*Adverse effects of imiquimod treatment: patients reported side effects and side effects noticed at clinical investigation.

*20 weeks follow-up*Treatment compliance: amount of applied doses of imiquimod, as documented by the study subject on a dose calendar.Histological presence and grading of CIN for the experimental arm.Adverse effects of imiquimod treatment: patients reported side effects and side effects noticed at clinical investigation.Quality of life for all patients.

*6, 12, 24 months follow-up*Cervical cytology outcomes for all patients, including HPV genotyping.Quality of life for all patients at 12 months follow-up

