### Statistical methods

Logistic regression analysis will be used to evaluate treatment efficacy of imiquimod treatment, compared to LLETZ treatment. Covariates in this analysis are age at diagnosis, CIN grade, smoking and HPV-subtype. Analysis will be based on intention-to-treat protocol. A biomarker prediction model for adequate response to imiquimod treatment will be developed by backward logistic regression analysis of biomarkers based on likelihood ration tests. The prevalence and severity of side effects of imiquimod and LLETZ treatment will be presented as proportions and means with 95 % confidence intervals. Differences in the rates of overall side-effects and severe side-effects between the imiquimod and LLETZ arms will be tested with a chi-square test. Disease recurrence rates after 6, 12 and 24 months will be evaluated in successfully treated patients by use of multiple logistic regression analysis, after adjustment for age at diagnosis, CIN grade, smoking, sexual behaviour and HPV subtype. Repeated-measures analysis of variance will be used to test for between-group differences over time in Quality of Life scores. Analysis of covariance will be used to compare group scores on these outcomes at 20 weeks and at 12 months, with adjustment for baseline scores.

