### Substantial amendment

The current study protocol includes a substantial amendment to the original study protocol, which consisted of three study arms: imiquimod treatment arm, LLETZ treatment arm and an observational arm. The purpose of the observational arm was to assess spontaneous regression of high-grade CIN and to develop a prognostic biomarker panel to predict spontaneous regression of high-grade CIN. Patients in the observational arm underwent no treatment for a period of maximum 20 weeks. Histological assessment of disease development was performed after 10 and 20 weeks by colposcopy with diagnostic biopsies. Inclusion of patients into the study was hampered by the observational arm: patients declined the study because they wished to be treated, rather than undergo observational management. The observational arm was removed from the study.

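### Backward elimination over up to 12 markers, with roughly 15 to 19 non-responders expected, is an unstable way to build the biomarker model that is a primary objective

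*Protocol article*

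**What the plan says.** Under Study objectives and outcome measures, the second primary item is "Development of a biomarker model to predict adequate response to imiquimod treatment". Statistical methods fixes the method: "A biomarker prediction model for adequate response to imiquimod treatment will be developed by backward logistic regression analysis of biomarkers based on likelihood ration tests". No retention p-value is given.

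Data collection lists the baseline markers in two groups:
- Immune: "markers of lymphoproliferative response: CD4, CD8, CD25, CD138, fox p3".
- Cell cycle: "cell cycle markers: p16, Rb, p53, Ki67, CK 13, CK 14, IMP3".

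The same section restricts them: "Histological biomarkers on biopsies of patients in the experimental arm". HPV genotyping is also recorded at baseline.

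Sample size calculation derives 42 per arm from the efficacy comparison (73% against 95%) and raises it to 53 for withdrawal. It then goes to 70 per arm on account of secondary outcomes. No stated figure sizes the biomarker model.

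**The concern.** Backward elimination starts from the full set of candidates and drops the weakest in turn. When the smaller outcome group is barely larger than the candidate list, the starting model is close to saturated. Which markers survive then depends heavily on chance, the surviving coefficients are too large, and performance measured in the same women is too good.

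This affects one of the two primary objectives. The Background gives individualised treatment as the eventual purpose, so a marker retained by chance could later count for or against offering non-surgical treatment to particular women. The efficacy comparison with LLETZ is not affected.

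**Working it through.** **1. The plan's own figure.** For 73% against 95%, two-sided 5%, 80% power, pooled variance, with mean proportion 0.84:

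n = [1.96 × √(2 × 0.84 × 0.16) + 0.842 × √(0.73 × 0.27 + 0.95 × 0.05)]² / 0.22² = (1.016 + 0.416)² / 0.0484 ≈ 42.4.

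This rounds up to 43, against the stated 42 (power at 42 is 79.6%). For withdrawal, 42 / 0.80 = 52.5, which gives 53 as stated. The figure is reproduced, and it concerns efficacy only.

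**2. Candidates.** 5 immune + 7 cell-cycle = 12 markers. HPV genotype would add to this if entered.

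**3. Women and non-responders.** 70 randomised to imiquimod; 70 × 0.80 = 56 after withdrawal. Non-responders = n × (1 − response rate).

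| Response rate | n = 56 | n = 70 | Per marker (÷ 12) |
|---|---|---|---|
| 73% (design rate) | 15.1 | 18.9 | 1.3 to 1.6 |
| 75% (top of hypothesised range) | 14.0 | 17.5 | 1.2 to 1.5 |
| 50% (bottom of hypothesised range) | 28.0 | 35.0 | 2.3 to 2.9 |

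**4. Selection from pure noise.** As a rough guide, 12 independent tests give at least one hit with probability 1 − 0.95¹² = 46% at p = 0.05 and 1 − 0.90¹² = 72% at p = 0.10.

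The procedure itself was simulated with 12 independent standard normal markers unrelated to outcome. The marker with the smallest likelihood-ratio statistic was removed until all that remained passed the retention threshold. There were 5,000 runs per row at 0.05 and 800 at 0.10. Both thresholds are assumptions.

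| n, response | Retention p | At least one kept | Two or more kept | Median apparent AUC when any kept |
|---|---|---|---|---|
| 56, 73% | 0.05 | 55% | 24% | 0.73 |
| 70, 73% | 0.05 | 52% | 21% | 0.70 |
| 56, 73% | 0.10 | 78% | 49% | 0.74 |
| 70, 73% | 0.10 | 77% | 49% | 0.71 |
| 70, 50% | 0.05 | 51% | 18% | 0.67 |
| 70, 50% | 0.10 | 78% | 45% | 0.68 |

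The true AUC is 0.50 in every row. With markers correlated at 0.3 and 73% response, at least one was kept in 57% (n = 56) and 50% (n = 70) of runs at 0.05, and in 81% and 80% at 0.10. More non-responders lower the apparent AUC somewhat but hardly change how often noise is selected.

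**5. When some markers are real.** With three truly predictive markers, backward elimination gave an apparent AUC of 0.77 to 0.81, against 0.59 to 0.63 in new data, with a calibration slope near 0.3. Ridge regression gave 0.62 to 0.64 in new data, with a slope near 1.1 to 1.3. The size of this gap depends on the signal strength assumed, so these figures illustrate the direction and order of the effect.

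**The case against.** **Much of the false selection comes from having 12 candidates rather than from backward elimination.** This stands. Twelve separate single-marker tests at p < 0.05 gave at least one hit in 50% (n = 56) and 48% (n = 70) of simulated trials, against 53% and 52% for backward elimination in the same exercise. Cross-validated LASSO still kept a noise marker in 33% and 28%. The case against backward elimination therefore rests more on inflated coefficients and apparent performance than on the count of false selections.

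**The article does not say that all 12 markers enter one starting model.** This is also fair. Data collection lists what is recorded, Statistical methods says only biomarkers, and p16 staining already contributes to the CIN diagnosis. The all-12 reading is an assumption. Candidate reduction, the retention threshold, shrinkage and internal validation may be in the full protocol or analysis plan, so their absence here is no finding. The selection method, however, is stated.

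**Pure noise is a worst case.** The Background says earlier biomarker models partially predicted the behaviour of CIN lesions. The three-marker simulation answers this: with real signal present, the apparent result is still far too good.

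Three stronger readings are tempting, and the documents do not support them:
- A reader might infer that the method will usually find predictors in noise. That depends on an unstated threshold. At 0.05 it is about an even chance.
- A reader might infer that the model will fail elsewhere. Some markers may carry signal, and no passage commits to using the model without further validation.
- A reader might infer that removing the untreated comparator invalidates the model. The amendment is disclosed ("The observational arm was removed from the study"), with its recruitment reason, and no change of selection method would restore that arm. It is a separate design limit and supports only a point of wording.

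**Conclusion.** The point holds in a limited form. The protocol commits a primary objective to backward likelihood-ratio elimination where, if all 12 listed markers are candidates, there are about 1.3 to 1.6 non-responders per marker at the design rate and 1.2 to 2.9 over the hypothesised range. Under that assumption selection will be unstable, and coefficients and apparent performance inflated.

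The size rests on continuous, normally distributed markers (the article does not give their scale) and on assumed retention thresholds. The direction of the conclusion does not change across the response rates and correlation examined. The sponsor should change the method.

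A secondary wording point follows from the design. The model is fitted in one treated arm, so it describes regression under imiquimod. It cannot separate that from spontaneous regression, which the Background puts at about 20–40% of high-grade lesions.

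**What to change.** In Statistical methods, replace backward elimination with penalised logistic regression, for example ridge, either on all candidate markers or on a short list named before outcome data are examined. Bootstrap the whole modelling process, including tuning and any selection. Report the optimism-corrected AUC and calibration slope as the result. Label the model exploratory, and describe it as a model of regression under imiquimod.

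This needs no extra women, visits or assays, and changes nothing in clinical management; the cost is analysis wording and computing time. The downside is that reported performance will be less flattering and fewer markers may be highlighted. Ridge keeps every marker and LASSO can still keep noise, so penalisation reduces the problem without removing it at this number of non-responders. The exploratory label is therefore needed as well.

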Secondary study objectives and outcome measures are:To determine the incidence and severity of side effects of LLETZ and imiquimod therapy, scored by the Common Terminology Criteria for Adverse Events guidelines.To estimate disease recurrence rates for both arms at 6, 12 and 24 months follow-up, defined as abnormal cervical cytology. The follow-up term starts after treatment is finished.To assess Quality of life (QoL) for both arms before, during and after treatment (at 0 and 20 weeks and after 1 year) by the following QoL questionnaires: [1] Medical Outcomes Study 36-Item Short-Form General Health Survey (RAND 36), to assess generic health-related quality of life, [2] the European Organization for Research and Treatment of Cancer (EORTC) QLQ-C30, to assess cancer-specific health-related quality of life, and [3] the European Organization for Research and Treatment of Cancer (EORTC) QLQ-CX24, to assess cervical cancer specific quality of life, including sexual functioning.

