Patients in the experimental arm are treated with imiquimod 5 % cream during 16 weeks. Imiquimod 5 % cream is administered in a vaginal applicator, containing 12,5 mg of imiquimod (one sachet). The cream is administered three times per week. The cream is administered by patients themselves at night, before going to bed. A vaginal shower is performed in the morning in order to remove cream remainders. In case of mild systemic drug-related side effects, patients are offered a prescription for anti-inflammatory drugs (paracetamol or NSAID). In case of more severe or persistent systemic or severe local side effects (Common Terminology Criteria for Adverse Events grade 2 or higher), the frequency of imiquimod application is decreased to twice per week, and subsequently to once per week if side effects persist. Imiquimod treatment is discontinued if side effects are unacceptable to patients hereafter. Subjects should use adequate contraception in order to prevent pregnancy. Subjects should not have vaginal sexual intercourse from the time of application of the imiquimod cream until the vaginal shower the next morning. A control colposcopy with diagnostic biopsies is performed after 10 weeks to rule out disease progression. Biopsies are performed at the initial high-grade CIN lesion site and at any other suspect site, with a minimum of two. In case of progressive disease (defined as increase in lesions size with stable disease grade, higher disease grade or invasive disease), surgical excision is performed.

Treatment efficacy for the experimental arm is evaluated at 20 weeks follow-up, by colposcopy with diagnostic biopsies. Biopsies are performed by using a cervical biopsy specimen forceps (Aesculap ER055R), at the initial high-grade CIN lesion site and at any other suspect site, with a minimum of two. In case of persistent or progressive disease (> CIN 1), surgical excision is performed.

Patients in the standard treatment arm undergo LLETZ at short term (within 4 weeks after the diagnosis). Excision of the transformation zone and macroscopic lesions is performed by a monopolar loop electrode, under local anaesthesia. A summary of study interventions can be found in Fig. 1.

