### Ethical considerations and dissemination

The study was approved off by the Medical Ethical Committee of Maastricht University Hospital, University of Maastricht. The study will be performed according to the standards outlined in the Declaration of Helsinki. Ethics committee approval has been completed. Monitoring of the study is performed by a Data and Safety Monitoring Board, appointed by the Clinical Trial Center Maastricht. Adverse events are recorded and reported according to local protocol. Study results will be offered for publication in an international medical journal. Study results will be communicated to trial participants by mail, if agreed upon by the participant.

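### The between-arm test of side-effect rates compares four examined assessments on imiquimod with one self-report after LLETZ, and excisions in the imiquimod arm have no scheduled side-effect record

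*Protocol article*

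**What the plan says.** All references are to the protocol article.

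- **Objective.** Under Study objectives and outcome measures, a secondary aim is: "To determine the incidence and severity of side effects of LLETZ and imiquimod therapy, scored by the Common Terminology Criteria for Adverse Events guidelines".
- **Test.** Statistical methods: "Differences in the rates of overall side-effects and severe side-effects between the imiquimod and LLETZ arms will be tested with a chi-square test". The section does not limit the comparison to a time point or a source of report.
- **Imiquimod data.** Data collection, week 6: "Adverse effects of imiquimod treatment: patient reported side effects and side effects noticed at clinical investigation". The entry is repeated at weeks 10, 14 and 20: "Adverse effects of imiquimod treatment: patients reported side effects and side effects noticed at clinical investigation".
- **LLETZ data.** Data collection, week 6 only: "Adverse effects of LLETZ treatment: patient reported side effects, using a standardized report form".
- **Excision in the imiquimod arm.** Interventions, on the 20-week biopsies: "In case of persistent or progressive disease (> CIN 1), surgical excision is performed". Excision is also performed for progression at the 10-week colposcopy.
- **After week 20.** The 6-, 12- and 24-month entry has "Cervical cytology outcomes for all patients, including HPV genotyping", plus quality of life at 12 months. It has no side-effect item.
- **General recording.** Ethical considerations and dissemination: "Adverse events are recorded and reported according to local protocol".

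**The concern.** The proportion of women with any recorded side effect depends on how often they are asked, over what period, and whether a clinician also looks. The two arms differ in all three respects. A chi-square test of the recorded proportions cannot separate a difference in tolerability from a difference in observation.

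The missing record after excision pulls the other way. Women whose disease does not regress on imiquimod go on to surgery, and no side-effect collection is scheduled for that surgery. The trial's rationale is to avoid surgical complications, so the surgical burden of the imiquimod strategy is exactly what a reader would want counted.

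Side effects are a secondary outcome. However, the Discussion makes them one of the two parts of clinical applicability, alongside quality of life. Records that were never collected cannot be recovered at the analysis stage.

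**Working it through.** **Plan's own figure.** There is none for this test. The Sample size calculation section says that roughly 70 per arm were needed for the secondary outcomes but gives no inputs, so nothing can be reproduced. I use its 70 per arm.

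**Schedule side by side (Data collection)**

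| | Imiquimod | LLETZ |
|---|---|---|
| Week 6 | report + examination | report on form |
| Week 10 | report + examination | none listed |
| Week 14 | report + examination | none listed |
| Week 20 | report + examination | none listed |
| After excision | none listed | week-6 form |

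**Women with an excision but no scheduled record.** The plan expects 50–75 % regression, so 25–50 % are due for excision: 70 × 0.25 = 17.5 (about 18) and 70 × 0.50 = 35. At the 73 % used for the sample size, 70 × 0.27 = 18.9 (about 19). Withdrawals are ignored.

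**Effect on the test.** The documents give no detection rates, so those below are assumptions. Each result is the exact probability that an uncorrected chi-square test at two-sided 5 %, with 70 per arm, rejects when the true side-effect risk is equal in both arms.

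(a) Same true rate of 40 %, detected in 95 % of affected women on imiquimod. The expected imiquimod proportion is 0.40 × 0.95 = 0.38.

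| LLETZ detection | Expected LLETZ proportion | Rejection |
|---|---|---|
| 95 % (equal) | 0.38 | about 5 % |
| 90 % | 0.36 | about 6 % |
| 80 % | 0.32 | 11 % |
| 70 % | 0.28 | 24 % |
| 50 % | 0.20 | 66 % |

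(b) Four imiquimod visits correlated within a woman, so worth only two looks. The proportion ever reporting is 1 − (1 − p)², against p for one LLETZ look.

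| p per look | Imiquimod v LLETZ | Rejection |
|---|---|---|
| 5 % | 9.8 % v 5 % | 19 % |
| 10 % | 19 % v 10 % | 33 % |
| 20 % | 36 % v 20 % | 57 % |

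(c) Four fully independent looks, with LLETZ women carrying the same risk per interval through week 20, unrecorded. The proportion is 1 − (1 − p)⁴.

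| p per look | Imiquimod v LLETZ | Rejection |
|---|---|---|
| 5 % | 18.5 % v 5 % | 73 % |
| 10 % | 34.4 % v 10 % | 95 % |

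If 20 % withdraw (70 × 0.8 = 56 per arm), the results in (c) become 63 % and 90 %.

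These models cover only unequal detection. Unrecorded excision effects lower the imiquimod total and cannot be quantified from the documents.

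**The case against.** **Closer monitoring of imiquimod is reasonable.** It is self-applied for 16 weeks, and application frequency depends on graded side effects. This stands. The fault is not the monitoring but the use of unequal data in a between-arm test.

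**LLETZ is a single procedure.** The Background describes pain, discharge and bleeding as short-term complications, so new imiquimod symptoms at weeks 10 to 20 may be real incidence rather than artefact. This stands, and it is why scenario (c) is an extreme. A reader might infer that the test would nearly always be falsely significant. The documents do not support that, because it needs independent visits and a LLETZ risk that continues unrecorded to week 20.

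**The test might use week 6 only.** Statistical methods does not say that all visits are pooled, and an unseen analysis plan could restrict the window. That is fair, but the present wording sets no restriction. Even at week 6 the imiquimod record adds clinical examination. An analysis plan can discard data but cannot supply LLETZ records that were not collected.

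**The methods overlap more than the schedule suggests.** The abstract mentions a standardized form without limiting it to one arm, and both therapies are graded by the same toxicity criteria. This narrows the difference in reporting method. It does not remove the extra examination or the four-to-one count.

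**Excision effects are not wholly lost.** A reader might infer that they never reach the imiquimod total. That is too strong. Adverse events are recorded under the local protocol, and the week-14 and week-20 visits follow any week-10 excision, although those entries are labelled as effects of imiquimod. What can be said is that no collection specific to excision is scheduled.

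**Conclusion.** The unequal ascertainment is written into the plan and bears directly on a named test. Because extra looks raise the imiquimod rate while unscheduled excision records lower it, the net bias cannot be signed or sized from the documents. With equal true risk, the false-positive probability runs from about 6 % when detection is nearly the same, through 19–33 % for two effective looks at 5–10 % each, to 73–95 % in the extreme case only. All of these rest on assumed detection rates. They treat overall side effects; severe ones may depend less on repeated looks.

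The primary efficacy analysis, the biomarker model, recurrence and quality of life are unaffected. This should be fixed as an inexpensive improvement to a secondary outcome; it does not threaten the trial's main conclusion.

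**What to change.** 1. Base the between-arm chi-square test only on the same patient-reported form at the same time points in both arms. LLETZ women still in follow-up can complete it by post or online.
2. Where that is not possible, restrict the test to the week-6 patient-reported items common to both arms.
3. Report examination findings and the additional imiquimod visits descriptively.
4. Use the existing LLETZ form after any excision in the imiquimod arm. Report those events as a separate, descriptive intention-to-treat total for the strategy. Keep them outside the common-window test, since an extra form for these women would make the looks unequal again.

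**Cost.** A few extra forms, with no added visits or procedures. Recruitment began in December 2014 (Trial status), so women already past a time point cannot supply that form. A week-6-only test covers only part of the 16-week imiquimod exposure and should be reported as such.

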**Methods/design:**

The study design is a randomized controlled trial. One hundred forty women with a histological diagnosis of high-grade CIN (CIN 2–3) will be randomized into two arms: imiquimod treatment during 16 weeks (experimental arm) or immediate LLETZ (standard care arm). Treatment efficacy will be evaluated by colposcopy with diagnostic biopsies at 20 weeks for the experimental arm. Successful imiquimod treatment is defined as regression to CIN 1 or less, successful LLETZ treatment is defined as PAP 1 after 6 months. Disease recurrence will be evaluated by cytology at 6, 12 and 24 months after treatment. Side-effects will be evaluated using a standardized report form. Quality of life will be evaluated using validated questionnaires at baseline, 20 weeks and 1 year after treatment. Biomarkers, reflecting both host and viral factors in the pathophysiology of CIN, will be tested at baseline with the aim of developing a predictive biomarker profile for the clinical response to imiquimod treatment.

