### Interventions

After informed consent is obtained, patients are equally randomized into one of two arms:*Experimental arm*. Patients in this arm are treated by a 16-week regime of imiquimod 5 % cream.*Standard arm*. Patients in this arm receive standard treatment by LLETZ.

Follow-up visits are anchored to the start of the treatment (either imiquimod or LLETZ). Cytological assessment will be performed by two independent trained cytology analysts, according to the Papanicolaou system. In case of inconsistent results, a consensus will be reached by discussion. The histopathological assessment of cervical biopsies will be performed by two independent pathologists according to national guidelines, based on the WHO guidelines. In case of inconsistent results, a consensus will be reached by discussion. CIN diagnosis will be based on evaluation of histological features concerned with differentiation, maturation and stratification of cells and nuclear abnormalities, in combination with p16 staining. In CIN 1 there is good maturation with minimal nuclear abnormalities and few mitotic figures. Undifferentiated cells are confined to the deeper layers (lower third) of the epithelium. Mitotic figures are present, but not very numerous. Cytopathic changes due to HPV infection may be observed in the full thickness of the epithelium. CIN 2 is characterized by dysplastic cellular changes mostly restricted to the lower half or the lower two-thirds of the epithelium, with more marked nuclear abnormalities than in CIN 1. Mitotic figures may be seen throughout the lower half of the epithelium. In CIN 3, differentiation and stratification may be totally absent or present only in the superficial quarter of the epithelium with numerous mitotic figures. Nuclear abnormalities extend throughout the thickness of the epithelium. Many mitotic figures have abnormal forms.

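### LLETZ recurrence at 6 months is zero by construction, because recurrence is analysed only in women whose success was itself a normal 6-month smear

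*Protocol article*

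**What the plan says.** Four statements in the protocol article bear on this.

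- **Recurrence outcome** (Study objectives and outcome measures, secondary): "To estimate disease recurrence rates for both arms at 6, 12 and 24 months follow-up, defined as abnormal cervical cytology". The same item adds: "The follow-up term starts after treatment is finished".
- **LLETZ success** (same section, primary): "Successful treatment for the LLETZ arm is defined as normal cytology at 6 months follow-up". The abstract puts it as "successful LLETZ treatment is defined as PAP 1 after 6 months".
- **Imiquimod success** (same section, primary): "Successful treatment for the experimental (imiquimod) arm is defined as regression to CIN 1 or less in diagnostic biopsies at 20 weeks follow-up".
- **Recurrence analysis set and model** (Statistical methods): "Disease recurrence rates after 6, 12 and 24 months will be evaluated in successfully treated patients by use of multiple logistic regression analysis", with adjustment for age, CIN grade, smoking, sexual behaviour and HPV subtype.

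Under Data collection, the 6-, 12- and 24-month entry reads: "Cervical cytology outcomes for all patients, including HPV genotyping". Cytology is thus planned in every woman, whether or not treatment succeeded.

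**The concern.** An analysis set should not be defined by the outcome it is used to measure. In the LLETZ arm, entry to the recurrence analysis and the 6-month recurrence outcome are one smear read in opposite directions. In the imiquimod arm, entry is decided by histology at 20 weeks and the outcome by a later smear, so events remain possible. The restriction removes events from one arm only.

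Recurrence is a secondary outcome, but the Background and Discussion name long-term efficacy and recurrence among the reasons for doing the trial. A reader shown a LLETZ 6-month recurrence of 0% beside a non-zero imiquimod rate would take as a finding what the definitions guarantee.

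**Working it through.** The plan gives no figure for recurrence, so there is none to reproduce. The check has three parts.

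**1. The definitions side by side**

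| | LLETZ | Imiquimod |
|---|---|---|
| Entry to the recurrence set | Normal cytology, 6 months | CIN 1 or less on biopsy, 20 weeks |
| 6-month recurrence | Abnormal cytology, 6 months | Abnormal cytology, 6 months |
| Can an entrant have the event? | No | Yes |

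Timing does not separate entry from outcome in the LLETZ arm. The secondary objective starts the clock at the end of treatment, while Interventions anchors visits to its start. LLETZ is a single procedure, so both give the same 6-month visit. For imiquimod, the 6-month smear falls at about week 26 counted from the start, or about week 16 + 26 = 42 counted from the end. Either is after the 20-week biopsy.

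**2. Size at 6 months**

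Inputs from Sample size calculation: 70 per arm, 73% imiquimod success, 95% LLETZ success, about 20% withdrawal.

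- Withdrawal before success assessment (assumption): 70 × 0.80 = 56 per arm. Entrants: 56 × 0.73 ≈ 41 imiquimod and 56 × 0.95 ≈ 53 LLETZ.
- No withdrawal: 70 × 0.73 ≈ 51 and 70 × 0.95 = 66.5, taken as 66.
- LLETZ women removed for an abnormal 6-month smear: 70 × 0.05 = 3.5. The LLETZ 6-month abnormality rate would be about 5% in all randomised women at the plan's own figure, and is exactly 0% under the stated rule.

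With k events, all in the imiquimod arm, the probability of that table is C(n_I, k) / C(n_I + n_L, k). For k up to 4 this is the two-sided Fisher p, because the opposite extreme table is more probable.

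- 2/41 v 0/53: (41 × 40)/(94 × 93) = 0.19
- 4/41 v 0/53: (41 × 40 × 39 × 38)/(94 × 93 × 92 × 91) = 0.033
- 3/51 v 0/66: (51 × 50 × 49)/(117 × 116 × 115) = 0.080
- 4/51 v 0/66: (51 × 50 × 49 × 48)/(117 × 116 × 115 × 114) = 0.034

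Four abnormal smears among imiquimod successes are enough under either denominator. The chance of four or more depends on the true 6-month abnormal rate in that group, which the documents do not give:

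| Assumed rate | 41 women | 51 women |
|---|---|---|
| 5% | 15% | 25% |
| 10% | 60% | 76% |
| 15% | 88% | 96% |
| 20% | 98% | 99.5% |

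These chances would be the same if the rate among all randomised LLETZ women were equally high, because the rule hides LLETZ events.

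A logistic model with an arm term, fitted to an illustrative 5/51 v 0/66, did not converge: log-odds ratio about 29.5, standard error about 950,000.

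**3. 12 and 24 months**

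LLETZ recurrence can now occur, but the sets are about 73% of one arm and 95% of the other, chosen by different tests at different times. Two mechanisms pull in opposite directions.

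- *Favouring LLETZ:* women abnormal at 6 months are removed from that arm only. If recurrence is counted cumulatively, with assumed equal rates of 10% by 6 months and 5% new by 12 months, imiquimod shows 1 − 0.90 × 0.95 = 14.5% and LLETZ shows 5%.
- *Favouring imiquimod:* the success filter removes about 27% of imiquimod women but only 5% of LLETZ women, so the imiquimod set is the more heavily selected.

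The protocol specifies neither cumulative counting nor the rates, so the net effect cannot be derived.

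**The case against.** The strongest reply is that no between-arm test of recurrence is written. Statistical methods names the arm contrast for efficacy, side effects and quality of life, but not in the recurrence sentence, and the objective is to estimate rates in both arms. That is correct. An arm contrast is a reasonable inference from an adjusted logistic model, no more, and the empty-cell problem depends on it. Read purely as description, though, the LLETZ 6-month rate is still fixed at zero and uninformative.

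Second, recurrence ordinarily presupposes clearance, so relapse among responders is a legitimate question. Women with more than CIN 1 at 20 weeks go on to excision, so an all-randomised analysis answers a different question. This stands, and is why the success-only rate should be kept as description.

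Third, imiquimod successes are not unscreened: they have passed colposcopy with at least two biopsies. This also stands, and is one reason why the direction of bias at later times is open.

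The intention-to-treat statement does not rescue the recurrence analysis, which sets its own population. Nor is this a detail left to an analysis plan, since the protocol itself fixes the definitions, time points, set and model.

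**Conclusion.** The point holds at 6 months as a matter of definition and needs no assumption: LLETZ recurrence is 0% by construction, imiquimod recurrence is not. Any 6-month arm comparison would be uninterpretable. The illustration of 4/41 v 0/53 (p = 0.033) rests on the plan's success rates and on all withdrawal preceding success assessment; dropping that last assumption changes little (4/51 v 0/66, p = 0.034).

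At 12 and 24 months the conclusion is weaker: an arm comparison would lack the protection of randomisation, with bias of unknown size and direction.

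Three stronger readings are not supported.

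- A reader might infer that every recurrence contrast is biased against imiquimod. The later contrasts have no derivable direction.
- A reader might infer that the 6-month result must always favour LLETZ. With no imiquimod events it would not, and 2/41 v 0/53 gives only p = 0.19.
- A reader might take the 73% regression and 47% complete remission quoted in the Background and infer that (73 − 47)/73 = 36% of imiquimod successes carry residual CIN 1 that would be called recurrence. That requires the gap to be CIN 1, to persist, and to show as an abnormal smear in every such woman; the protocol states none of these.

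The outcome is secondary. The primary efficacy analysis, sample size and recruitment are untouched, but the recurrence paragraph is wrong as written and should be corrected before analysis.

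**What to change.** Reword the recurrence paragraph in Statistical methods.

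- **Between-arm comparison:** abnormal cytology at 6, 12 and 24 months in all randomised women by intention to treat, at one Pap threshold stated for both arms. Count it regardless of later excision and report it beside the proportion needing excision. The 6-month comparison need not be dropped, because it is well defined in this population.
- **Success-only analysis:** keep it as a descriptive within-arm relapse rate, counting only smears taken after that arm's success assessment. For LLETZ this means smears after the 6-month one; for imiquimod, those after the 20-week biopsies.

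The cost is one paragraph of wording. No new visits, samples or patients are needed, because cytology at these times is already planned for everyone. The real downside is that the intention-to-treat rate describes the treatment strategy, including excision after failed imiquimod, rather than relapse after a documented response; the descriptive rates address the latter within each arm.
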